### 2.5. Materials

The usability tests will be conducted in a laboratory environment that simulates two areas commonly found in hospital wards: (i) a fully equipped treatment room, where nurses commonly prepare intravenous drugs; (ii) a fully equipped single-bed patient room. Both areas contain audio/video recording equipment, allowing for a panel of evaluators to follow the tests in real time, without direct interaction with the participants, and for posterior analyses. The tests will be performed using an upper arm simulator that allows for PIVC insertion and drug administration (Multi-Venous IV Training Arm Kit; Nasco Healthcare, Fort Atkinson, WI, USA). This is a lifelike adult arm reproduction with a multi-vein system designed for peripheral intravenous therapy in the antecubital fossa or dorsum of the hand, with median, basilic, and cephalic accessible and palpable veins that allow intravenous peripheral therapy simulation (Figure 2). The study protocol ensures that all participants received standardized instructions and materials to perform the usability test.

The double-chamber syringe was developed with a 20 mL size: 10 mL for drug chamber (blue plunger) and 10 mL for flush solution chamber (white plunger). This innovative double-chamber syringe enables the filling (none of the chambers are pre-filled) and administration of both solutions (verification of the catheter patency through the administration of the flush solution, the subsequent drugs delivery, and the final flushing of the catheter using the remaining flush solution) [32]. With the double-chamber syringe, the instructions for use will be provided to the participants, which will be also assessed by the participants in the interviews/focus groups.

Supplementary materials will be used, such as (i) the informed consent document, with a brief description of the study, the main purpose of the groups, and the voluntary nature of participation; (ii) non-disclosure agreement (NDA); (iii) anonymous demographic questionnaire to sample characterization; (iv) interviews and focus groups guidelines (Table 2); and (v) usability questionnaire (42 items in a 7-point Likert scale focused on significant usability dimensions: usefulness, ease of use, ease of learning, satisfaction, and intention to use).

### 2.6. Interventions

This pre-clinical validation will be assessed through a two-arm parallel RCT in two phases (Figure 1), in which the nurses will be requested to perform intravenous drug administration per the allocated arm in the simulated setting. In order to ensure the standardized conditions for the procedure, the PIVC is already in place (being placed always by the same nurse of the research team). In the first phase (intra-subject analyses), the 20 nurses will perform the protocol using the two types of syringes, starting with the double-chamber syringe and, then, a standard syringe (arm A), or in reversed order (arm B). In the second phase (inter-subject analysis), another 20 nurses (without any previous information or contact with this double-chamber syringe) will be allocated to perform the protocol with a double-chamber syringe (arm A) or with standard syringes (arm B). The usability test session will be run as a single participant test, with each participant repeating the procedure three times, under external supervision. The procedure is divided in two main phases (drug preparation and drug administration), and tasks were defined in accordance to both study groups (Table 3 and Table 4). The procedure will be recorded by audio/video for posterior analyses. At the end of the usability tests, interviews/focus group with all participants will be conducted to collect detailed qualitative information about this new medical device.

### 2.7. Outcomes

These usability tests are intended to measure primary (effectiveness, efficiency, and safety) and secondary outcomes (satisfaction and intention of use), ensuring that the medical device accomplishes the needed legal requirements before testing in real clinical settings. Specifically, in this pre-clinical study, the primary outcomes that will be measured are: (i) number of tasks and goals achieved; (ii) procedure execution time; and (iii) number, type, and intensity of errors (Table 5). These parameters will be extracted from the video recordings (usability tests) and compared to a detailed procedure checklist. The secondary outcomes will be assessed through the usability questionnaire and audio recordings from the individual interviews and focus group carried. As the participants perform each procedure three times (with the double-chamber syringe and standard syringes), the research team can also analyze their learning curve and training needs required to use this new medical device, along with the qualitative (interviews and focus group) and quantitative (usability questionnaire).

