### 2.8. Data Collection, Management, and Analysis

Study participants identification numbers (ID) will be used, and all data will be anonymized for subsequent analysis and reports/publications. Individual information to be collected includes demographic (gender, age), academic qualifications (degree), and professional data (clinical experience, work setting) of the nurses eligible to perform the usability tests. The names of the participants on the consent forms will be stored separately in locked cabinets accessible only by named personnel.

Statistical analysis of the collected data will be performed using the Statistical Package for the Social Sciences, version 24 (IBM SPSS Statistics 24; SPSS Inc., Chicago, IL, USA). Means, standard deviations, frequencies, and percentages will be used as descriptive statistics (or median values and interquartile ranges for skewed data). The outcomes in the two groups in each study phase will be examined to detect the effect of group allocation through inferential statistics (Student’s t-test for independent and paired samples, or non-parametric equivalents, Mann-Whitney U and Wilcoxon tests; X^2^ test or Fisher’s exact test), considering a statistical significance level of 0.05 (two-sided significance level of 5%). Qualitative content analysis will also be conducted after the transcription of the individual interviews and focus group.

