Phase 1 (Drug Preparation)	Determine the total drug dose to be administered according to chart prescription. Check the drug ampule for intactness, cloudiness, particles, and color. Gently flick or tap the top of the ampule to remove medication trapped in the top of the ampule. Wrap a 2 in. × 2 in. gauze pad around the neck of the ampule, snap the top off, breaking it. Discard the top in a sharps container. Attach a 18G filter needle to a 10 mL syringe. Withdraw the medication from the ampule. Hold the syringe vertically and draw 0.2 mL of air into the syringe. Remove the filter needle and attach a blunt 18G needle. Eject the 0.2 mL of air and read the dose. Attach a blunt 18G needle to a 10 mL syringe. Remove the neck of a plastic ampule containing 0.9% normal saline for catheter flush. Discard the neck. Withdraw 10 mL of normal saline from the ampule. Hold the syringe vertically and draw 0.2 mL of air into the syringe. Eject the 0.2 mL of air and read the dose. Label both syringes. Prepare a tray with the syringes, pair of clean gloves, sterile gauze, and a 2% chlorhexidine gluconate in 70% isopropyl alcohol spray.	Determine the total drug dose to be administered according to chart prescription. Attach a 18G filter needle to the syringe. Remove the neck of a plastic ampule containing 0.9% normal saline for catheter flush. Discard the neck. Withdraw 10 mL of normal saline from the ampule to the white plunger chamber. Hold the syringe vertically and draw 0.2 mL of air into the syringe. Eject the 0.2 mL of air and read the dose. Check the drug ampule for intactness, cloudiness, particles, and color. Gently flick or tap the top of the ampule to remove medication trapped in the top of the ampule. Wrap a 2 in. × 2 in. gauze pad around the neck of the ampule, snap the top off, breaking it. Discard the top in a sharps container. Withdraw the medication from the ampule to the blue plunger chamber. Hold the syringe vertically and draw 0.2 mL of air into the syringe. Remove the filter needle and attach a blunt 18G needle. Eject the 0.2 mL of air and read the dose. Label the syringe. Prepare a tray with the double-chamber syringe, pair of clean gloves, sterile gauze, and a 2% chlorhexidine gluconate in 70% isopropyl alcohol spray.

**Table 4 ijerph-17-08376-t004:** Procedures to be accomplished by the study participants: drug administration.

	Standard Syringe	Double-Chamber Syringe

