Phase 2 (Drug administration)	Don clean gloves. Disinfect the catheter hub with the 2% chlorhexidine gluconate in 70% isopropyl alcohol spray. Place a sterile gauze below the catheter hub. Holding the flushing syringe, remove both the needle and the cap, and place them on a sterile surface. Insert the flush syringe into the catheter hub. Administer a 5 mL flush to clear the line with a push–pause technique. Continue to hold the catheter hub and apply positive pressure on the plunger. Remove the flush syringe, attach the needle, and place it on a sterile surface. Insert the drug syringe into the catheter hub. Administer the prescribed drug. Continue to hold the catheter hub and apply positive pressure on the plunger. Remove the drug syringe. Holding the flushing syringe, remove both the needle and the cap. Insert the flush syringe into the catheter hub. Administer a 5 mL flush to clear the line with a push–pause technique. Remove the flush syringe. Remove the sterile gauze. Leave the patient room.	Don clean gloves. Disinfect the catheter hub with the 2% chlorhexidine gluconate in 70% isopropyl alcohol spray. Place a sterile gauze below the catheter hub. Holding the flushing syringe, remove both the needle and the cap, and place them on a sterile surface. Insert the double-change syringe into the catheter hub. Administer a 5 mL flush to clear it with a push–pause technique. Continue to hold the catheter hub. Apply positive pressure on the drug chamber’s plunger and administer the prescribed dose. Continue to hold the catheter hub. Apply positive pressure on the flushing chamber’s plunger. Administer a 5 mL flush to clear the line with a push–pause technique. Remove the double-chamber syringe. Remove the sterile gauze. Leave the patient room.

**Table 5 ijerph-17-08376-t005:** Types of errors to be assessed during the study.

Phase 1 (Drug Preparation)	Phase 2 (Drug Administration)

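### The first primary outcome is a raw count of tasks achieved, but the two devices have task lists of different length, so the count favours the standard syringe even when nurses perform equally well

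*Protocol article*

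**What the plan says.** Section 2.7 names three primary outcomes, of which the first is "i) number of tasks and goals achieved". On scoring it adds: "These parameters will be extracted from the video recordings (usability tests) and compared to a detailed procedure checklist". It does not say that the number achieved is divided by the number required.

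Section 2.6 makes the task lists specific to the device: "tasks were defined in accordance to both study groups (Table 3 and Table 4". Each table has one column for the standard syringe and one for the double-chamber syringe.

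Section 2.6 also separates the phases. In phase 1, 20 nurses use both devices and the arms are the two orders of use. In phase 2, another 20 nurses use one device each.

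Section 2.8 gives the analysis: "The outcomes in the two groups in each study phase will be examined to detect the effect of group allocation through inferential statistics". The tests listed are independent and paired t-tests, their non-parametric equivalents, and chi-square or Fisher tests, at two-sided 0.05. None is assigned to a particular outcome. Percentages appear only in a general list of descriptive statistics.

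**The concern.** A count of tasks achieved compares devices fairly only if both procedures offer the same number of tasks. Here they do not. The standard procedure needs a second syringe, with its own preparation step ("Attach a blunt 18G needle to a 10 mL syringe") and an exchange at the hub ("Remove the flush syringe, attach the needle, and place it on a sterile surface. Insert the drug syringe into the catheter hub"). It makes three hub insertions where the double-chamber procedure makes one.

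A nurse who does everything right with the new device therefore scores lower than a nurse who does everything right with standard syringes. Taken as written, this primary outcome could show the new device as less effective when there is no difference in performance, and could hide a real advantage. Fewer catheter manipulations, which the Discussion presents as a benefit of the device, lower its score on this outcome.

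**Working it through.** **Inputs from the protocol article.** Task lists: Tables 3 and 4. Group sizes: 10 per arm, 20 per phase (section 2.2). Phase 1 within nurse, phase 2 between nurses (section 2.6). Two-sided alpha 0.05 (section 2.8). The article states no task totals. Its only related figure, 40 participants, reproduces as 10 × 2 arms × 2 phases = 40.

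**Assumed, because not stated.** Per-task success p = 0.80, 0.90 or 0.95, the same for both devices; correlation of tasks within a nurse (intraclass correlation, ICC) 0, 0.05 or 0.10; one procedure per nurse and device.

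**Step 1: count the tasks, one per sentence.**

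| | Standard | Double-chamber |
|---|---|---|
| Preparation (Table 3) | 18 | 17 |
| Administration (Table 4) | 18 | 14 |
| Total | 36 | 31 |

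The split matters a little. The double-chamber column twice writes holding the hub and pressing the plunger as separate sentences, for example "Continue to hold the catheter hub. Apply positive pressure on the drug chamber’s plunger and administer the prescribed dose". The standard column joins the two actions in one sentence. Merging them alike gives 12 for administration and 17 + 12 = 29 in total. The gap is 36 − 31 = 5, or 36 − 29 = 7.

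**Step 2: consequence without any statistical assumption.** Flawless runs score 36 and 31. A standard run that misses four tasks scores 36 − 4 = 32, still above a flawless double-chamber run at 31. With 29 as the maximum, a standard run could miss six (36 − 6 = 30) and still score higher.

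**Step 3: expected gap at equal performance.** Gap = (36 − 31) × p = 4.0, 4.5 and 4.75 tasks for p = 0.80, 0.90 and 0.95. Put the other way, at p = 0.80 the standard mean is 36 × 0.80 = 28.8, and the double-chamber syringe needs 28.8/31 = 0.929 success to equal it. At p = 0.90 the standard mean is 32.4, which exceeds 31 and cannot be equalled.

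**Step 4: chance of a significant result with no performance difference.** Counts were drawn as binomial(36, p) and binomial(31, p). For ICC ρ > 0, each nurse's success rate was drawn from a beta distribution with parameters p(1 − ρ)/ρ and (1 − p)(1 − ρ)/ρ. In phase 1 the nurse has the same rate for both devices. There were 20,000 simulated trials per setting.

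| p | Phase 2, ICC 0 | Phase 2, ICC 0.05 | Phase 2, ICC 0.10 | Phase 1 paired, any of these ICCs |
|---|---|---|---|---|
| 0.80 | 0.955 | 0.618 | 0.434 | 0.999 |
| 0.90 | 1.000 | 0.903 | 0.750 | 1.000 |
| 0.95 | 1.000 | 0.988 | 0.928 | 1.000 |

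Cross-check for phase 2, ICC 0, p = 0.80: SD = √[(36 + 31)/2 × 0.80 × 0.20] = √5.36 = 2.315; standard error = 2.315 × √(2/10) = 1.035; 4.0/1.035 = 3.86; normal approximation Φ(3.86 − 1.96) ≈ 0.97, in line with 0.955.

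**Step 5: sensitivity to the split.** With 36 vs 29, the phase 2 rates at ICC 0.10 are 0.718, 0.941 and 0.991. With a gap of only three tasks (36 vs 33, for illustration), they are 0.193, 0.382 and 0.672, and the phase 1 rates run from 0.865 to 1.000. All are well above 0.05.

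**Step 6: the same simulations with achieved/applicable as the outcome (36 vs 31).** The expected difference is 0. Rejection rates are 0.040 to 0.052 in phase 2 and 0.046 to 0.052 in phase 1.

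**The case against.** The strongest reply is that the scoring instrument is not shown. Comparing a recording with a device-specific checklist can mean achieved against required. Percentages and chi-square or Fisher tests are on the list in section 2.8, no test is tied to this outcome, and a condensed article may leave the scoring rule to the full protocol. The goals are not listed and could be the same for both devices, and tasks could be scored in larger units than sentences.

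Part of this stands. The totals of 36 and 31 are a reading of unnumbered tables, and a raw-count test is the plain reading of the outcome, not an explicit instruction. But the outcome is stated as a number, and nothing in the article turns it into a proportion. Equal goals would not cancel unequal tasks within the same count, and the extra syringe exchange remains under any sensible split.

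Two stronger readings are tempting and should not be drawn:

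- A reader might infer that the randomised arms differ by construction throughout the trial. In phase 1 every nurse performs both procedures, so both arms contain the same tasks; the built-in gap lies between devices within nurse. Only in phase 2 does it lie between arms.
- A reader might infer that a false rejection is practically certain. In phase 2, rates above 99% at 36 vs 31 were obtained only with independent tasks and success of 0.90 or more. Tasks done by one nurse are plausibly correlated, and the rates then fall.

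It is also fair to say that fewer steps may show as a gain in execution time, another primary outcome, and that the bias runs against the new device, so it would not create a false claim of benefit.

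**Conclusion.** The concern holds. As stated, the first primary outcome has a maximum of about 36 for the standard syringe and about 31 (or 29) for the double-chamber syringe, so equal performance produces an expected deficit of about 4 to 5 tasks for the new device (36 vs 31, success 0.80 to 0.95). The unequal maxima follow from the tables alone.

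The rejection rates are conditional on the assumed success rates and correlations: in phase 2 about 96% to 100% with independent tasks and about 43% to 93% with an ICC of 0.10; in phase 1 nearly all trials. The three repetitions per nurse were not modelled. Averaging them would leave the expected gap unchanged.

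The documents do not show that an unadjusted count will in fact be tested. They show that the outcome as written leads to one, and that no denominator is given.

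**What to change.** In section 2.7, define the effectiveness outcome as the percentage of the tasks applicable to that device that are completed correctly per procedure (achieved/applicable), and state the number of applicable tasks for each device. Use this outcome for both the paired comparison in phase 1 and the unpaired comparison in phase 2. If goals are counted, list them and score them separately.

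Add a sensitivity analysis limited to tasks that appear in both columns, such as hub disinfection, the flush before and after the drug, drug delivery and labelling. This guards against the device-specific tasks being easier or harder than the shared ones, which a percentage does not correct. Report the difference in the number of required steps separately, as a description of the device.

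The cost is a sentence or two in section 2.7 and a denominator column on the checklist. No new participants, recordings or changes to the procedures are needed. The rule should be fixed before the recordings are scored, because the trial is unblinded and the choice between count and percentage can change the direction of the result.

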### 2.8. Data Collection, Management, and Analysis

Study participants identification numbers (ID) will be used, and all data will be anonymized for subsequent analysis and reports/publications. Individual information to be collected includes demographic (gender, age), academic qualifications (degree), and professional data (clinical experience, work setting) of the nurses eligible to perform the usability tests. The names of the participants on the consent forms will be stored separately in locked cabinets accessible only by named personnel.

Statistical analysis of the collected data will be performed using the Statistical Package for the Social Sciences, version 24 (IBM SPSS Statistics 24; SPSS Inc., Chicago, IL, USA). Means, standard deviations, frequencies, and percentages will be used as descriptive statistics (or median values and interquartile ranges for skewed data). The outcomes in the two groups in each study phase will be examined to detect the effect of group allocation through inferential statistics (Student’s t-test for independent and paired samples, or non-parametric equivalents, Mann-Whitney U and Wilcoxon tests; X^2^ test or Fisher’s exact test), considering a statistical significance level of 0.05 (two-sided significance level of 5%). Qualitative content analysis will also be conducted after the transcription of the individual interviews and focus group.

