## 2. Materials and Methods

### 2.1. Study Design

A two-steps parallel randomized controlled trial (RCT, Figure 1) with two arms was designed (involving standard syringes currently used in clinical practice and the new double-chamber syringe), following the Consolidated Standards of Reporting Trials (CONSORT) 2010 recommendations [28,29,30]. Considering that this project comprises the development of a new medical device, the EU directives [15], implemented in Portugal by the Portuguese National Authority of Medicines and Health Products (INFARMED), and ISO Standards [16,17,18,19,20] were considered. The pre-clinical study is planned to last 3 months from the start of the recruitment process (in July 2020).

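### Phase 1 is a two-period crossover labelled as a parallel trial; its stated contrast is order of use, and the implied paired test leaves the period effect unadjusted

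*Protocol article*

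**What the plan says.** Section 2.1 of the protocol article gives one design label for the whole study: "A two-steps parallel randomized controlled trial (RCT, Figure 1) with two arms was designed". Section 2.6 repeats it for both phases and then describes two different designs.

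- Phase 1: "In the first phase (intra-subject analyses), the 20 nurses will perform the protocol using the two types of syringes". The arms are defined by order: "starting with the double-chamber syringe and, then, a standard syringe (arm A), or in reversed order (arm B").
- Phase 2: another 20 nurses "will be allocated to perform the protocol with a double-chamber syringe (arm A) or with standard syringes (arm B").

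Section 2.8 covers both phases with one sentence on the contrast: "The outcomes in the two groups in each study phase will be examined to detect the effect of group allocation through inferential statistics". It lists independent and paired t-tests, Mann-Whitney, Wilcoxon, and "X^2^ test or Fisher’s exact test", all at a two-sided 5% level, and does not assign tests to phases. Neither period nor sequence is mentioned. Section 2.4 specifies simple 1:1 randomization. Section 2.7 expects to study a learning curve over three repetitions.

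**The concern.** The word arm means device in Phase 2 and order of use in Phase 1. One sentence about the effect of allocation cannot serve both phases. Applied to Phase 1 as worded, it compares nurses who used the two syringes in one order with nurses who used them in the other, and that carries no information on the device.

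The natural fallback is a paired test of DUO against standard. It does address the device, but it treats the first and second blocks of procedures as exchangeable. A nurse's second block on the same simulator may well go faster or with fewer errors whichever syringe is used. A paired test puts that shift into the error term and, when the two orders are unequally filled, into the device estimate as well.

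At stake is the Phase 1 device comparison on the primary outcomes, from half of the participants (20 of 40).

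**Working it through.** **The plan's own figure.** 10 per arm × 2 arms × 2 phases = 40, as section 2.2 states. The 10 per arm rests on the chance of detecting a usability problem. The documents give no power, effect size, SD or period effect, so those below are assumptions.

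**Step 1: the contrast as worded.** Take a nurse's outcome as nurse effect + device effect + period effect + error. Averaged over both uses, a nurse in either arm has had each device once and each period once. The arm A minus arm B difference therefore has expectation zero whatever the device does. In simulation (20 nurses, 40,000 trials) with a true device effect of one residual SD, the mean difference was 0.00 and rejection was 5%.

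**Step 2: the plain paired test.** Let D = DUO minus standard within a nurse, with SD 1 once device and period are taken out. Let tau be the device effect and pi the period effect (second block minus first), both in that unit.

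- Arm A (DUO first): mean of D = tau − pi. Arm B: tau + pi.
- Mean of D over all nurses = tau + pi × (nB − nA)/20.
- Expected sample variance of D = 1 + pi² × 4·nA·nB/(20 × 19).

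At 10:10 the bias is zero, but the variance is 1 + 1.053·pi² (400/380 = 1.053). At pi = 1 it is 2.05, so the standard error is √2.05 = 1.43 times what it need be. Simulated power for tau = 0.7 at 10:10:

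| pi | paired t-test | period-adjusted |
|---|---|---|
| 0.25 | 83% | 84% |
| 0.5 | 77% | 84% |
| 1 | 56% | 84% |

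**Step 3: unequal sequences.** With simple randomization of 20 nurses, P(exactly 10:10) = 184,756/1,048,576 = 17.6%.

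| Split | P(this or worse) | size of bias | type I error, pi = 0.5 | pi = 1 |
|---|---|---|---|---|
| 12:8 | 50.3% | 0.2 pi | 4.4% | 2.9% |
| 13:7 | 26.3% | 0.3 pi | 6.5% | 7.5% |
| 14:6 | 11.5% | 0.4 pi | about 10% | about 16% |

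Averaged over all splits, type I error is about 5% at both values of pi.

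**Step 4: period adjustment.** Take each nurse's first-block minus second-block difference. Its mean is tau − pi in arm A and −tau − pi in arm B. Half the difference between arms is tau, and pi cancels at any split. An independent t-test on these differences kept type I error at 5%.

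**Step 5: categorical outcomes.** If X² were used to compare devices in Phase 1, the same 20 nurses would supply both columns. With event probability 0.3 and latent correlation 0.3 or 0.6 (assumed), the true size of a nominal 5% test is about 3% or 1.4%. The test is conservative and loses power.

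**The case against.** Several points on the other side stand.

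- A reader might infer that Phase 1 will test order and never the device. The documents do not support that. Section 2.6 labels Phase 1 as intra-subject and Phase 2 as inter-subject, and the paired t and Wilcoxon tests in 2.8 have no natural use in Phase 2. The wording of the contrast is wrong, but a within-nurse device comparison is probably meant.
- A reader might infer that no listed test can remove the period effect. That is also too strong. The listed independent t or Mann-Whitney test does so when applied to period differences (step 4). What is missing is any statement that it will be used this way.
- A reader might infer a general excess of false positives. At 10:10, the number per arm planned in 2.2, the paired estimate is unbiased. Averaged over splits, type I error is nominal, and clear inflation needs a split near 14:6.
- Section 2.8 does not assign X² or Fisher to Phase 1. They are legitimate in Phase 2.
- The learning curve in 2.7 mainly concerns repetitions and training with the new device, and participants must already have experience of intravenous administration (Table 1). The size of any between-block effect is undocumented, and at pi = 0.25 the loss is negligible.
- The study is sized to find usability problems, and Phase 2 gives a device comparison free of order effects.

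It could also be said that the choice of analysis variable belongs in a statistical analysis plan. That answers the missing detail. It does not answer the design label and the contrast, which the article states and which conflict with its own description of Phase 1. Nor does the average over splits settle the bias: the split will be known once nurses are randomized, and the estimate is then off by a fixed fraction of the period effect.

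**Conclusion.** The point holds in a limited form. Phase 1 is a randomized two-period crossover, it is called parallel in 2.1 and 2.6, and the contrast that 2.8 names for it is order of use. The test most likely intended, a plain paired one, compares devices but takes no account of period.

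The cost depends on a period effect that the documents do not give. Under the assumptions above it runs from almost nothing (83% against 84% power at pi = 0.25) to substantial (56% against 84% at pi = 1), with a bias of 0.2 to 0.4 pi at splits from 12:8 to 14:6. These figures assume normal outcomes, one summary value per nurse and device, and no unequal carry-over. The correction should be made, but the matter does not invalidate the study.

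**What to change.** - **2.1 and 2.6:** describe Phase 1 as a randomized two-period crossover, and keep the parallel label for Phase 2.
- **2.8, Phase 1 contrast:** name DUO versus standard within nurse, adjusted for period. Use the already listed independent t or Mann-Whitney test on within-nurse period differences between sequences, or a mixed model with device, period and sequence and a random nurse effect.
- **2.8, Phase 1 binary outcomes:** use a period-adjusted paired test such as Mainland-Gart. McNemar alone respects the pairing but not the period.
- **2.8, Phase 2:** keep the direct independent-group device comparisons, including X² and Fisher, for this phase.

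The cost is rewording and one degree of freedom, with no new nurses, data or procedures. If there is no period effect and the split is uneven, power falls slightly: about 81% against 85% at 13:7, for a device effect of one residual SD (1/√2 = 0.71 SD of the within-nurse difference).

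This does not remove unequal carry-over between the syringes, and a carry-over check with 20 nurses would have little power. The report should state that as a limitation.

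### Phase 1 is a crossover, but its stated analysis either compares the two orders of use or runs a paired test that ignores order

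*Protocol article*

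**What the plan says.** Section 2.1 labels the whole study as parallel: "A two-steps parallel randomized controlled trial (RCT, Figure 1) with two arms was designed". Section 2.6 repeats the label ("This pre-clinical validation will be assessed through a two-arm parallel RCT in two phases") but then describes two different designs.

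- **Phase 1:** "In the first phase (intra-subject analyses), the 20 nurses will perform the protocol using the two types of syringes". The arms are distinguished by sequence alone: "starting with the double-chamber syringe and, then, a standard syringe (arm A), or in reversed order (arm B". This is a two-period, two-sequence crossover.
- **Phase 2:** a fresh set of 20 participants is used, and they "will be allocated to perform the protocol with a double-chamber syringe (arm A) or with standard syringes (arm B". This is a parallel comparison.

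Section 2.8 gives one inferential sentence for both phases: "The outcomes in the two groups in each study phase will be examined to detect the effect of group allocation through inferential statistics". The tests it lists include the "t-test for independent and paired samples, or non-parametric equivalents, Mann-Whitney U and Wilcoxon tests", together with chi-square or Fisher tests, at a two-sided 5% level. It mentions neither order nor period.

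Two other statements bear on the point. Section 2.7 has each procedure done three times and notes that "the research team can also analyze their learning curve and training needs required to use this new medical device". Section 2.4 specifies simple 1:1 randomization, while section 2.2 plans 10 nurses per arm.

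**The concern.** In Phase 1 arms A and B differ only in which syringe comes first. Both arms contain the same mix of double-chamber and standard runs, so comparing them tests order and not device.

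If a paired device comparison is meant instead, order is left out of it. A nurse completes three runs on the first device before starting the second, and the tasks overlap heavily. Table 3 lists 18 preparation steps for the standard syringe and 17 for the double-chamber syringe, and each of the 17 has a standard counterpart. Some practice gain from the first device to the second is therefore to be expected, above all in execution time, a primary outcome. In the double-chamber-minus-standard difference this gain has opposite signs in the two arms.

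At stake is the Phase 1 device comparison for time, tasks and errors. Its confidence interval is too wide if the orders are balanced, and its estimate is shifted if they are not. The randomized order, which allows a common period effect to be removed, goes unused.

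**Working it through.** **The plan's own figure.** 10 nurses × 2 arms × 2 phases = 40, as section 2.2 states. The size comes from a problem-detection formula. No power, SD or effect size is given, so there is no power figure to reproduce.

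**Model.** Let δ be the device effect (double-chamber minus standard) and π the period effect (first minus second device). Let the nurse-level difference have SD 1. Then

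- arm A (double-chamber first): d = δ + π + error
- arm B (standard first): d = δ − π + error

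Assumptions, since the article gives no values: normal errors, δ = 0.7 SD, π = 0, 0.5, 1 and 1.5 SD, no carry-over that differs by order, and 20 nurses.

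**Reading 1: compare arm A with arm B.** Each nurse's mean over both devices contains the two device levels in equal parts, so δ cancels from the arm contrast. In simulation at 10:10 this test rejects in 5.1% of trials at a device effect of 0.66 SD and in 5.1% at 1.5 SD. It has no power for the device at all.

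**Reading 2: plain paired t-test on d (19 df).** The comparator is the order-adjusted estimate (mean d in A + mean d in B)/2, with the pooled within-order SD, 18 df and standard error √[(1/n_A + 1/n_B)/4].

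*Equal orders, 10:10.* The paired mean is unbiased, but its variance estimate absorbs the period effect: the expected sample variance of d is 1 + π² × 20/19. At π = 1 this is 2.05, an SD of 1.43 where 1 is correct, so the interval is about 43% too wide.

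| π (SD) | Power, paired | Power, adjusted | Type I error, paired |
|---|---|---|---|
| 0 | 0.84 | 0.84 | 5% |
| 0.5 | 0.78 | 0.84 | 2.9% |
| 1.0 | 0.56 | 0.84 | 0.6% |
| 1.5 | 0.27 | 0.84 | 0.1% |

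*Unequal orders.* The bias of the paired mean is π × (n_A − n_B)/20. At 13:7 that is π × 6/20 = 0.3π. If times shorten with practice, a surplus of nurses using the double-chamber syringe first makes it look slower, and a surplus using it second makes it look faster. With π = 1 SD:

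| Split | Size of bias (SD) | Type I error, paired |
|---|---|---|
| 10:10 | 0 | 0.6% |
| 12:8 | 0.20 | 2.9% |
| 13:7 | 0.30 | 7.5% |
| 14:6 | 0.40 | 16.5% |

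At 13:7 and π = 1 the paired power for δ = 0.7 is 0.93 or 0.15, depending on which order is larger. At π = 0.5 it is 0.92 or 0.56. The adjusted test keeps about 0.81 power and 5% type I error in each case. Its standard error is √[(1/13 + 1/7)/4] = 0.234, against √[(1/10 + 1/10)/4] = 0.224 at 10:10.

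*How likely the splits are.* Under simple randomization of 20, exactly 10:10 has probability C(20,10)/2²⁰ = 17.6%. A split of 12:8 or worse has probability 50.3%, and 13:7 or worse 26.3%.

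*Averaged over all splits.* At π = 1 the paired power is 0.54 to 0.55 across simulation runs, against 0.82 adjusted. The paired type I error averages 4.9% to 5.0%.

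**The case against.** The strongest reply is that 2.8 is loosely worded rather than wrong. Section 2.6 labels Phase 1 as intra-subject and Phase 2 as inter-subject, and 2.8 lists both paired and independent tests, so the natural mapping is paired tests for Phase 1. A condensed article may leave period adjustment to a fuller document. That mapping is fair and disposes of the literal reading as the likely intent. It does not rescue the plan: the sentence applies the allocation contrast to each phase, and the paired test it would leave for Phase 1 is still not the right one for this design.

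Several further points stand as limits.

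- The bias depends on the realised split. If 10 per arm were enforced, only the power loss would remain, and the paired test would err on the cautious side. Averaged over simple randomization its type I error is about 5%.
- The size of the period effect is assumed. At 0.5 SD and 10:10 the loss is modest, 0.84 to 0.78.
- The nurses already have experience of intravenous administration, the step order differs between devices, and the learning curve in 2.7 concerns repeated runs. Transfer between devices is plausible but not quantified.
- The simulation uses normal data. It fits time better than task and error counts.
- Order adjustment removes a common period effect only. If learning carries over differently in the two orders, the adjusted estimate is biased, but the plain paired estimate is exposed to this as well.
- The protocol claims no power, which lowers the urgency.

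**Conclusion.** The concern holds. Neither reading of 2.8 gives a sound Phase 1 device comparison: the allocation test measures order, and the paired test leaves the period effect in the error term and, with unequal orders, in the estimate. With 20 nurses, a difference SD of 1, a device effect of 0.7 SD and a period effect of 1 SD, power at 10:10 is 0.56 instead of 0.84. At 13:7 the estimate is off by 0.3 SD. With no period effect nothing is lost, and at 0.5 SD the loss at 10:10 is about 6 percentage points. The direction of the problem follows from the design. Its size rests on assumed values that the article cannot confirm. Because the study is not sized on power, this is a change that should be made rather than a fatal flaw, but it touches every primary outcome in Phase 1.

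**What to change.** In 2.8, replace the Phase 1 analysis with wording such as: *For each nurse, the outcome is averaged over the three runs with each device, and the first-used minus second-used difference is taken. The device effect is half the difference between arm A and arm B in the mean of these differences, with a 95% confidence interval and a two-sample t-test, or a Mann-Whitney U test on the same differences. The period effect is reported alongside.*

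This isolates the device because the expected difference is δ + π in arm A and −δ + π in arm B, and half the gap between them is δ. For yes/no outcomes, Fisher's exact test can be applied to the discordant nurses, classified by order and by which period had the event.

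Confine the allocation contrast to Phase 2. Do not use the Phase 1 comparison of arm means as a device test or as a preliminary test for carry-over. In 2.1 and 2.6, call Phase 1 a crossover, and state that the adjusted estimate assumes no carry-over that differs by order. Blocked randomization would secure 10:10 and remove the bias, but it would not recover the power lost by the paired test, so the analysis needs to change in either case.

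The cost is wording and one degree of freedom. The tests are already listed in 2.8 and no new data are needed. If there is no period effect, power stays at about 0.84 at 10:10 and falls from 0.84 to about 0.81 at 13:7.
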